### Lifestyle interventions

Patients in the lifestyle intervention group will undergo an elaborate risk factor assessment at the nurse-led outpatient clinic. This assessment involves measuring body weight and length, blood pressure, a blood test for cholesterol and diabetes, and a home sleep apnoea test (HSAT). The HSAT is performed with a WatchPAT™ 300, which has previously been validated in a cohort of AF patients [30]. Furthermore, lifestyle behaviour such as physical inactivity, alcohol consumption and smoking are assessed in a structural interview. The risk factor definitions and treatment targets are presented in Table 2. If there are too many risk factors to be treated in a reasonable way for the patient (e.g., it would take too much time and effort), the physician will decide which risk factors will be treated, together with the patient in a shared-decision making approach. During the lifestyle intervention, patients will have approximately 3–5 physical appointments with the nurse–practitioner as well as a 10-min consultation with the cardiologist. Further additional consultations for risk interventions will take place as described in Table 2. The ablation will be scheduled when treatment targets are reached, or, if targets are not reached, at maximally 6 months after study enrolment.

**Table 2 Tab2:** Risk factor interventions and targets in the lifestyle intervention group

Risk factor definition	Target and intervention
Overweight: BMI ≥ 27 kg/m^2^	10% body weight reduction is targeted. Treatment consists of additional consultations with a dietician and a physical fitness and activity programme
Physical inactivity: less than 3,5 h of merely vigorous physical activity per week and limitations during activity	> 3.5 h of physical activity per week is targeted. This is supported by a physical fitness and activity programme guided by a physiotherapist or sport cardiologist
Excessive alcohol consumption: > 8 units a week for women and > 14 units a week for men	We aim for a reduction to ≤ 8 units a week for women and ≤ 14 units a week for men. This is supported by behaviour counselling
Tobacco consumption	Patients should quit smoking. A smoking cessation programme is conducted over 6 weeks by a certified nurse
Hypertension: > 130/90 mmHg	Target blood pressure is < 130/90 mmHg. The lifestyle interventions above and antihypertensive medication are used

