### Statistical analyses

Descriptive statistics will be used to report baseline characteristics of the study population. The primary and secondary endpoints can occur during the entire participation period, which is from baseline to ablation (in the intervention group during the risk treatment; in the control group when patients await the ablation) and in 12 months after the ablation. The different pre-ablation durations amongst patients lead to different study participation periods. Therefore, the number of events will be normalized using the participation period and will be reported in numbers per year (the event rate). The clinical hypothesis that the intervention group will have a lower event rate will be tested by fitting a Poisson regression model to the event data and testing the effect of the intervention group using a Wald test. Results will be reported in terms of incidence risk ratios with accompanying 95% confidence intervals. The primary analysis will be on an intention-to-treat basis. Subgroup analyses will be performed on the primary endpoint. Covariates of interest in this study include gender, age, type of AF (paroxysmal vs. persistent) and number and extent of the respective modifiable risk factors as defined in Table 2.

The secondary endpoints will be analysed by means of chi-squared test or Fisher’s exact test depending on the number of occurrences. Changes in weight and blood pressure will be compared using the appropriate test (unpaired *t* test or Mann–Whitney *U* test), depending on the distribution of data. Laboratory tests will be analysed for differences by fitting linear mixed models to the data.

A cost-effectiveness analysis will be included, covering incremental cost-effectiveness ratio (ICER) and an evaluation of change in patient value, using the EuroQol-5D and AFEQT questionnaires and healthcare-related costs of intervention. Differences in medical hospital costs for both study groups will be compared using the appropriate statistical test (unpaired *t* test or Mann–Whitney *U* test), depending on the distribution of data. Cost savings associated with the study intervention will be calculated by subtracting the cost of the intensive treatment from the cost of the conventional treatment. The completed EuroQol-5D, AFEQT and TBQ questionnaires will be analysed for differences between treatment groups at different moments by fitting linear mixed models to the data.

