### Sample size

The number of hospital admissions in the control group is estimated as 1.0 per patient per year [33, 34]. The proposed intervention is expected to reduce the primary endpoint with 30%. Taking the pre-ablation period into account, in the intervention group, we expect an overall event rate of 0.75 per patient per year. Assuming a balanced design with equal allocation of patients to the two groups, the minimum sample size to achieve an 80% power with 5% Type I error on the primary analysis is 144 (72 per treatment group). A total of 150 patients will be enrolled in this study, taking dropouts into account.

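### 72 patients per group do not give 80% power for 1.0 versus 0.75 events per patient-year; the planned two-sided Poisson Wald test has about 36–50%

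*Protocol article*

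**What the plan says.** The Sample size section gives the planning inputs in sequence.

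- Control rate: "The number of hospital admissions in the control group is estimated as 1.0 per patient per year".
- Effect: "The proposed intervention is expected to reduce the primary endpoint with 30" per cent. This is then diluted for the time before ablation: "in the intervention group, we expect an overall event rate of 0.75 per patient per year".
- Allocation: "Assuming a balanced design with equal allocation of patients to the two groups".
- Result: "the minimum sample size to achieve an 80% power with 5% Type I error on the primary analysis is 144 (72 per treatment group").
- Enrolment: "A total of 150 patients will be enrolled in this study, taking dropouts into account".

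The Statistical analyses section fixes the primary test. The hypothesis of a lower event rate is to be "tested by fitting a Poisson regression model to the event data and testing the effect of the intervention group using a Wald test", with results given as rate ratios with 95% confidence intervals and significance at p < 0.05. Events are counted over the whole participation period, which is the pre-ablation period plus 12 months. For the intervention group, the Lifestyle interventions section limits the pre-ablation period: ablation takes place when targets are met or, "if targets are not reached, at maximally 6 months after study enrolment".

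**The concern.** A comparison of two Poisson rates draws its information from the expected number of events. With 72 patients per arm and one to one and a half years of participation, the planned rates yield about 72 to 108 events in the control arm and 54 to 81 in the intervention arm. That is few events for a rate ratio of 0.75, so a claim of 80% power looked implausible.

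At stake is how a null result will be read. The plan declares a 20% chance of missing the planned effect. If the true chance is 50% or more, a non-significant result would be taken as evidence against the intervention when the trial was about as likely as not to miss the very effect it was designed to find.

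**Working it through.** **Inputs from the article.** Control rate 1.0 and intervention rate 0.75 per patient-year; 80% power; 5% type I error; 72 per arm (144 in total), 75 per arm as enrolled; Wald test in a Poisson model.

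**Inputs that must be assumed.** Mean participation T is not given. Twelve months after ablation sets a base of 1.0 year, and the 6-month limit in the intervention group adds at most 0.5 year there, so T was varied from 1.0 to 1.5 years in both arms. A value near 1.2 years follows if the rate is 1.0 before ablation and 0.70 after it: (x + 0.70)/(x + 1) = 0.75 gives x = 0.2 year. Sidedness is not stated either. The 95% confidence intervals and p < 0.05 point to a two-sided test; one-sided 5% was also tried.

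**Attempt to reproduce 72 per arm.** The requirement in patient-years per arm is

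(z_α + z_β)² × (1/1.0 + 1/0.75) / (ln 0.75)²

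- Two-sided: (1.960 + 0.8416)² × 2.3333 / 0.08276 = 221.3
- One-sided: (1.645 + 0.8416)² × 2.3333 / 0.08276 = 174.3

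Dividing by T and rounding up gives the patients needed per arm, before dropout:

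| Mean participation | Two-sided 5% | One-sided 5% |
|---|---|---|
| 1.0 year | 222 | 175 |
| 1.2 years | 185 | 146 |
| 1.5 years | 148 | 117 |

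The plan has 72. Formulas based on the rate difference, on square-root rates and on a Poisson-regression null variance were also tried, and none returns 72 per arm for a rate of 0.75.

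**Power with 72 per arm, rate ratio 0.75.** Power = Φ(|ln 0.75| / √(1/E₀ + 1/E₁) − z_α), where E₀ = 72 × T × 1.0 and E₁ = 72 × T × 0.75.

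| T | E₀ | E₁ | \|ln 0.75\|/SE | Two-sided | One-sided |
|---|---|---|---|---|---|
| 1.0 | 72.0 | 54.0 | 1.598 | 35.9% | 48.1% |
| 1.2 | 86.4 | 64.8 | 1.751 | 41.7% | 54.2% |
| 1.5 | 108.0 | 81.0 | 1.957 | 49.9% | 62.3% |

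With 1.2 years in control and 1.5 years in intervention, two-sided power is 46.0%. Simulation of the two-sided test with 400,000 replicates gave 35.9%, 41.8% and 50.1% for the three rows.

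**How far the inputs would have to move.**

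- Participation: 221.3 / 72 = 3.1 years per patient two-sided, or 174.3 / 72 = 2.4 years one-sided.
- Effect: with the undiluted rate of 0.70, two-sided power at 72 per arm is 49.3% to 66.2% over 1.0 to 1.5 years. One-sided with 1.5 years for everyone, it is 76.8%.

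**Power with all 150 enrolled and no dropout (75 per arm), rate ratio 0.75, two-sided.** 37.1%, 43.1% and 51.5% at 1.0, 1.2 and 1.5 years. The rate ratio detectable with 80% power is 0.59, 0.62 and 0.66 respectively.

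**The case against.** The strongest defence is that the article leaves mean participation and sidedness open, so no single power figure can be called the plan's own. The hypothesis is worded directionally, and the full protocol may hold details that the article omits. This stands as a limit on precision: 42–50% requires a two-sided test and 1.2 to 1.5 years, 36% applies at 1.0 year, and a one-sided test gives 48–62%. It does not rescue the claim, because every one of these values is well below 80%.

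One near match can also be cited in the plan's favour. A Poisson-regression sample-size formula with rate ratio 0.70, a one-sided test and 1.5 years for everyone gives 70 per arm. That replaces the stated 0.75 by 0.70, uses a different null variance and gives every patient the maximum participation. The planned Wald test has 76.8% power even there.

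Several stronger readings are tempting, and the article does not support them.

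- *That 144 was a per-arm figure mistaken for a total.* Requirements close to 144 per arm do arise (144 to 146 one-sided at 1.2 years, 146 to 148 two-sided at 1.5 years). Since different settings land there, the match identifies no cause.
- *That the 0.75 is itself inconsistent.* It follows from a 30% reduction after ablation and a mean pre-ablation period of 0.2 year (2.4 months). Six months is a maximum, so a shorter mean is allowed.
- *That the control rate refers to a wider set of admissions than the endpoint.* In context the wording reads naturally as shorthand for the primary endpoint, and the cited sources are not available to show otherwise.
- *That overdispersion lowers the power of the planned test further.* With model-based Poisson standard errors and a variance-to-mean ratio of 2 (an illustration, not a figure from the article), the rejection rate for 75 per arm at 1.5 years stays near 51%. What rises is type I error, to about 2 × [1 − Φ(1.96/√2)] ≈ 16–17%. Loss of power would apply to a dispersion-adjusted test, which the article does not specify.

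**Conclusion.** The sample-size statement is wrong as written. At the stated rates, 144 patients do not give 80% power under any reading tried. Two-sided power with 72 per arm is about 36–50% for a mean participation of 1.0 to 1.5 years, and the most favourable one-sided reading gives 62%. The two-sided requirement is two to three times the planned number (148/72 = 2.1; 222/72 = 3.1).

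The size of the shortfall rests on assumed participation and sidedness and on purely Poisson counts; its existence does not depend on the choice within those ranges. The finding concerns the power claim only. It does not show how the error arose, and it does not call the planning rates into question.

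**What to change.** Keep the enrolment of 150 and correct the Sample size section in one of two ways.

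1. State the sidedness and the assumed mean participation, and replace 80% with the power that follows. For 75 per arm without dropout, rate ratio 0.75 and a two-sided 5% test, this is about 37% at 1.0 year, 43% at 1.2 years or 51.5% at 1.5 years. Any dropout lowers these values.
2. Keep 80% and state the effect it applies to: a rate ratio of about 0.59 at 1.0 year, 0.62 at 1.2 years or 0.66 at 1.5 years (two-sided, 75 per arm, no dropout).

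Sidedness and mean participation are needed here only because the power figure cannot be corrected without them. The change is to wording and adds no patients, visits or procedures. Its price is a less favourable power statement, and a null result would then have to be read in that light, with the confidence interval for the rate ratio carrying the interpretation.

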## Summary

This POP trial will be the first study to test the effectiveness of a nurse-led clinic applying personalized risk factor management in a prospective randomized controlled trial on ablation outcomes. The trial is designed as a comparative effectiveness trial with the purpose of directly improving AF patient care by comparing a new treatment strategy with routine clinical care [35]. Current evidence is still limited to observational data or single risk factor treatment trials. The intervention includes screening for OSA and other AF-lifestyle factors, personalized lifestyle optimization, and the use of an e-health platform. The POP researchers hypothesize that in a high-risk population with at least one lifestyle AF-risk factor, the implementation of an integral AF management clinic is beneficial for ablation outcomes. Furthermore, the POP-trial will provide more conclusive evidence on the implementation of a multidisciplinary team in AF management.

## Conclusion

The POP study will evaluate the efficacy of a multidimensional lifestyle intervention treatment before ablation in patients with paroxysmal or persistent atrial fibrillation. The study will analyse the effect of this elaborate treatment on the number of hospitalizations for re-ablation and cardioversion.
